## Abstract

**Background:**

The office workplace is a key setting in which to address excessive sitting time and inadequate physical activity. One major influence on workplace sitting is the organizational environment. However, the impact of organizational-level strategies on individual level activity change is unknown. Further, the emergence of sophisticated, consumer-targeted wearable activity trackers that facilitate real-time self-monitoring of activity, may be a useful adjunct to support organizational-level strategies, but to date have received little evaluation in this workplace setting.

**Objective:**

The aim of this study is to evaluate the feasibility, acceptability, and effectiveness of organizational-level strategies with or without an activity tracker on sitting, standing, and stepping in office workers in the short (3 months, primary aim) and long-term (12 months, secondary aim).

**Methods:**

This study is a pilot, cluster-randomized trial (with work teams as the unit of clustering) of two interventions in office workers: organizational-level support strategies (eg, visible management support, emails) or organizational-level strategies plus the use of a waist-worn activity tracker (the LUMOback) that enables self-monitoring of sitting, standing, and stepping time and enables users to set sitting and posture alerts. The key intervention message is to ‘Stand Up, Sit Less, and Move More.’ Intervention elements will be implemented from within the organization by the Head of Workplace Wellbeing. Participants will be recruited via email and enrolled face-to-face. Assessments will occur at baseline, 3, and 12 months. Time spent sitting, sitting in prolonged (≥30 minute) bouts, standing, and stepping during work hours and across the day will be measured with activPAL3 activity monitors (7 days, 24 hours/day protocol), with total sitting time and sitting time during work hours the primary outcomes. Web-based questionnaires, LUMOback recorded data, telephone interviews, and focus groups will measure the feasibility and acceptability of both interventions and potential predictors of behavior change.

**Results:**

Baseline and follow-up data collection has finished. Results are expected in 2016.

**Conclusions:**

This pilot, cluster-randomized trial will evaluate the feasibility, acceptability, and effectiveness of two interventions targeting reductions in sitting and increases in standing and stepping in office workers. Few studies have evaluated these intervention strategies and this study has the potential to contribute both short and long-term findings.

## Introduction

### Background

The workplace is a key health promotion setting [1,2], with now extensive evidence demonstrating the effectiveness of interventions targeting physical activity in this environment [3]. Generally, physical activity programs in workplaces have had a beneficial impact on health risk biomarkers, work attendance, and job stress [3]. However, a common criticism has been that workplace physical activity interventions typically only reach those who are already fit and motivated to be active [4], and have had negligible impact on reductions in sitting [5,6]. These two issues may be addressed through a shift in focus to organization-wide interventions that have the potential to reach a greater proportion of employees than conventional individually centered approaches, and to interventions that target change across the activity spectrum including: sedentary time (sitting or lying with low energy expenditure, ≤1.5 metabolic equivalents (METS) [7]); light intensity activities (such as standing or incidental movement, >1.5 to <3 METS [8]); as well as moderate- and vigorous-intensity physical activities (MVPA, ≥3 to <9 METS [8]).

Sedentary and light intensity behaviors occupy much of the waking day [8], more than 95% on average in adults. The distribution of time spent between these two behaviors is increasingly being recognized as having potentially important implications for health and well-being [9,10]. Higher levels of light intensity activity are associated with improved blood glucose levels [11], physical health and well-being [12], and decreased depression [13]. Although several behaviors fall within the light intensity spectrum, there is preliminary evidence to suggest that even just postural shifts to standing could have some metabolic benefit [14,15]. In contrast, high levels of daily sitting time have been detrimentally associated with outcomes such as all-cause mortality, cardiovascular disease incidence and mortality, type 2 diabetes incidence [16,17], and cancer incidence and mortality [17], as well as risk indicators for these [18]. In addition, there is growing evidence suggesting that the manner in which sitting is accumulated may be important, with more breaks (or interruptions: either with activity or standing) in sedentary time showing beneficial associations with cardiometabolic indicators including waist circumference [15,19,20], blood glucose [15,19-22], insulin [21,22], and triglycerides [15,18-20].

### Sitting in the Workplace

For office workers, workplace sedentary time is a large contributor to overall sedentary time [23,24], with studies showing that office workers spend, on average, three-quarters of their work hours sitting [23-27]. Given this pervasive nature of sitting in the office, and that office workers are the largest individual occupational sector [28], the office workplace has been identified as a key setting to target reductions in sitting time [29].

Office workers generally have the advantage of being colocated, which means a wide range of influences can be targeted within intervention approaches. Based on workplace health promotion frameworks [1,30] and behavioral models for understanding sitting and activity [31,32], common influences are organizational, environmental, and individual factors, with the notion that individual-level strategies alone are unlikely to be sufficient for sustained behavior change [32]. Organizational-level strategies are seen as particularly important for program implementation [33], to change the culture of an organization [30,34], and for programs to be institutionalized into the organization and sustained [30]. Key organizational-level strategies include having management support for programs [33,34] and implementing the program from within the organization via dedicated onsite staff or workplace ‘champions’ [35].

Despite these frameworks, workplace interventions targeting MVPA have typically targeted the individual and not the organizational- or environmental-level influences [36,37]. Similarly, there have been very few studies that have implemented organizational-level strategies in workplace sitting interventions. The studies that have addressed the organizational level have done so in combination with individual-level strategies (eg, health coaching) and/or physical environment (eg, sit-stand workstation) strategies [27,38-41]. Findings from these multicomponent interventions have shown significant and large reductions in sitting both at the workplace (eg, −125 minutes/8-hour workday [38], −89 minutes/8-hour workday [39]) and across the whole day (eg, −66 minutes/day [40]). While organizational elements were reported as important in these studies [38,39], and a lack of management support reported as a key issue for those studies that have reported less success [27,41], no study to date has identified how much change results from the organizational-level component alone. If found to be effective, an added benefit of this organizational-level approach is that the intervention elements are minimal both in terms of cost and employee burden, which may be beneficial for organizations that have limited employee time or funds.

### Activity Trackers as Intervention Tools

While organizational-level strategies may be sufficient on their own, it is also important to consider individualized elements to possibly enhance the success of the intervention. Evidence suggests that individual, self-monitoring devices such as pedometers are a common element of successful workplace physical activity interventions [36,42] that can increase activity [43-48] and decrease sedentary time [43,44]. Recent advances in technology have seen the emergence of more sophisticated wearable activity trackers that go beyond just simple step counting to incorporate many of the strategies known to support behavior change [49]. Such strategies, including the provision of detailed, real-time feedback, long-term tracking, prompts, and goal setting, as well as the measurement of multiple behaviors, give activity trackers the potential to be effective behavior intervention tools [49,50]. Indeed, their potential as low-cost behavior change support tools has been recognized by several workplace wellness programs in the United States, where activity trackers are distributed to encourage employees to get healthy and reduce their insurance premiums [51,52].

There has been minimal research on the feasibility, acceptability, and effectiveness of activity trackers as intervention tools. A recent review highlighted the large heterogeneity in the small field of research studies and the mixed quality of the research [53]. However, there was some indication that activity trackers may lead to pre-post physical activity increases and are feasible to wear [53]. There was, however, very limited evidence for long-term physical activity increases [53]. In fact, only four studies out of the 11 in the review evaluated long-term outcomes (≥6 months), with only one study resulting in a significant change in physical activity [53]. There is even less evidence supporting the use of activity trackers to target sitting and standing: the activities that are most common in the office workplace setting [38,39]. As recently highlighted in a review [6], interventions that focus on increasing only physical activity do not necessarily result in changes in sitting; likewise, activity trackers that focus on steps and activity may not necessarily elicit changes in sitting time.

As such, the current study will pilot a waist-worn activity tracker (the LUMOback) that measures and notifies wearers of their sitting time, and also measures activities across the spectrum including number of steps and time spent standing, walking, and running [54]. Given the importance of organizational-level strategies [1,30], and the evidence suggesting self-monitoring tools are effective with additional strategies [42,53,55], the activity tracker will be implemented in conjunction with organizational-level support strategies. To evaluate whether the intervention strategies can also be sustained long-term, assessments will occur in the short (3 months) and long-term (12 months).

### Aims

The primary aims of this pilot study are to assess two interventions (organizational-level strategies only; organizational-level strategies plus an activity tracker) in office workers regarding their feasibility, acceptability, and short-term (3 month) effectiveness for sitting reduction. The primary effectiveness outcomes are sitting time at work and overall. Secondary aims are to examine the short-term effectiveness of the interventions for other activities, and health- and work-related outcomes; the relative effectiveness of the two interventions for changes in sitting time and other activities; predictors of changes in sitting and activity; and the long-term (12 month) feasibility, acceptability, and effectiveness of the interventions.

## Methods

### Design

A cluster-randomized design will be used, with data collection occurring at baseline, 3, and 12 months (see Figure 1). The cluster-randomized design (with work teams as the unit of clustering) was chosen to minimize contamination among participants from the two intervention groups. The trial has been approved by the University of Queensland Behavioural and Social Sciences Ethical Review Committee (approval number: 2014000089) and is prospectively registered with the Australian New Zealand Clinical Trials Registry [registration number: ACTRN12614000252617].

**Figure 1 figure1:**
[figure not shown]
Overview of study design, consent processes, intervention, and assessment elements.

### Participants

Participants will be office workers, recruited from work teams from two Australian capital cities (~1000-km apart) within the one organization, Lendlease, an international property and infrastructure group. Inclusion criteria are office-based workers, working at least 0.6 full-time equivalent (ie, at least 60% of full-time work hours) and ambulatory (able to walk at least 10 meters). Exclusion criteria are pregnancy at baseline, allergies to adhesive tape (Opsite and Hypafix required for assessments), and a planned absence from work for longer than 2 weeks during the first 3-month study period. Employees who have their own activity-permissive workstation at the baseline assessment will also be ineligible.

### Recruitment

#### Recruitment of Organization

The study liaison and workplace champion for the trial will be the Lendlease Head of Workplace Wellbeing ([name]). The workplace champion, located in Sydney (site A), will work in partnership with the research team to tailor the intervention to Lendlease and to create strong buy-in from senior management. Project staff will be based in Brisbane (site B).

#### Recruitment of Managers and Teams

Workplace teams (typically with 10-15 individuals in each team) will be selected from site A and site B by the workplace champion. Teams will be defined as having a line manager, being physically colocated, and having regular group meetings. Eligible teams will need to be desk-based and have a sufficient number of team members with access to a Bluetooth-enabled mobile phone required for the activity tracker to function. Team managers will be approached by the workplace champion for their consent.

#### Recruitment of Participants

Once the team manager has consented, the workplace champion will email individual team members the information sheet detailing the study and the required level of commitment, along with the consent form. Teams randomized to receive the activity tracker will receive additional details regarding the LUMOback. Interested team members will be invited to attend a face-to-face information session where they will have their eligibility assessed by project staff, and then be invited to sign the consent form and proceed to the baseline assessment. Initial consent will only be for baseline and 3-month assessments; participants will be invited to reconsent for the 12-month assessment (see Figure 1).

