### Randomization

Following manager consent, and prior to the information session, each team will be numbered randomly, using a random number generator, and then listed in numeric order. Teams will then be randomized to either Group 1 (organizational-level strategies only) or Group 2 (organizational-level strategies plus activity tracker), across location strata (site A and B) and team size strata within site A (small/large) using a randomization website [56]. The randomization schedule will be created by a university staff member not involved in the study. A project staff member will then apply the randomization schedule to the list of teams. Neither project staff nor participants will be blinded to participants’ randomization condition.

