A LUMOback and a four-page instruction booklet that covers an introduction to the device, set-up instructions, and frequently asked questions will be distributed to Group 2 participants by the workplace champion following baseline assessments. On receipt of the device, participants will be asked to download the free app and sync the LUMOback with their phone. Participants will be asked to use their work email to set up their device as this will later be used to request the data from the company LUMO Bodytech. Participants can wear the device as much or as little as they like and their self-directed usage will be tracked. However, participants will be instructed by project staff to wear their LUMOback during the 3-month assessment period both to gather validity data and to estimate the intervention effectiveness while wearing the LUMOback. Participants will be allowed to keep the LUMOback.

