### Sample Size

For this pilot study, the sample size was selected based on what the workplace deemed feasible (18 teams). With a usual team size of 10 to 15, and two-thirds expected to be eligible and participate (just over eight per team), we anticipate approximately 150 participants in total, with 75 randomized to each group. This sample size will provide adequate power (≥80% power) with 5% two-tailed significance, to detect short term (3 month) changes within groups (primary effectiveness aim) of our minimum difference of interest (MDI) in our primary outcomes of work and overall sitting time (see Table 2). All calculations are based on no multiple comparison adjustment to significance (in line with the exploratory nature of the study), an anticipated 30% attrition, and strong clustering (ICC=0.1) [58] with an anticipated design effect of 1.48 (ie, 1+0.1×4.83, with an average 5.83 participants per team). Under these same assumptions, power to detect changes equal to the MDIs for the secondary activity outcomes with 5% two-tailed significance are presented in Table 2 , along with the minimum detectable differences (MDDs) between groups for relative effectiveness (secondary aim). This pilot did not power a priori on other research questions, such as health outcomes and long-term changes (12 months). The MDIs and MDDs all reflected modest effects for activity. The assumptions regarding standard deviations (SD), pre-post correlations and clustering were informed by published and unpublished data from previous workplace interventions [38,58] and Australian population data from the AusDiab study.

**Table 2 table2:** Power to detect changes within groups (effectiveness) and minimum detectable differences between groups (relative effectiveness) with 5% significance, two-tailed.

Outcome	MDI^a^	Assumed values		Effectiveness	Relative effectiveness
		SD^b,c^	Pre-post *r* ^c^	Power	MDD^d^
Primary outcomes					
Work sitting time	45 minutes	90	0.6	90%	50 minutes
Overall sitting time	45 minutes	90	0.6	90%	50 minutes
Secondary outcomes					
Work prolonged sitting time	45 minutes	120	0.6	67%	65 minutes
Overall prolonged sitting time	45 minutes	120	0.6	67%	65 minutes
Work standing time	30 minutes	70	0.6	79%	35 minutes
Overall standing time	30 minutes	70	0.6	79%	35 minutes
Work stepping time	15 minutes	20	0.7	>99%	10 minutes
Overall stepping time	15 minutes	30	0.7	96%	15 minutes

^a^minimum difference of interest.

^b^standard deviation.

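### Teams are allocated before their members volunteer, are screened, consent and are measured at baseline, so the between-group (secondary) contrast is open to recruitment bias that the article does not acknowledge

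*Protocol article*

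**What the plan says.** The order of events comes from two sections of the protocol article, Recruitment of Participants and Randomization.

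- Managers consent first. Then: "Following manager consent, and prior to the information session, each team will be numbered randomly", and the teams are randomised within strata of site and, at site A, team size.
- The workplace champion emails members the information sheet and consent form. At this stage the material already depends on the arm: "Teams randomized to receive the activity tracker will receive additional details regarding the LUMOback".
- Interested members then meet project staff in person. Of that meeting the article says: "they will have their eligibility assessed by project staff, and then be invited to sign the consent form and proceed to the baseline assessment".
- On blinding: "Neither project staff nor participants will be blinded to participants’ randomization condition".
- Under Activity Tracker, the devices "will be distributed to Group 2 participants by the workplace champion following baseline assessments".

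Sample Size expects about two-thirds of members to be eligible and take part. Aims and Sample Size both class the comparison of the two interventions as secondary. Statistical Analyses adjusts that comparison for baseline values and for potential confounders, which are kept if associated with the outcome at P<.2. Methodological Considerations covers the missing control group, contamination, and the champion's choice of teams (as a limit on generalizability). It does not cover differences in individual recruitment between arms.

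**The concern.** In a cluster trial, randomising teams balances teams. It balances the individuals analysed only if entry to the study does not depend on the arm. Here members of tracker teams decide whether to join after receiving information that the other teams are not said to receive, and the staff who screen and enrol them know the allocation. If the prospect of a tracker attracts or deters a particular kind of member, the arms will contain different kinds of volunteer. The contrast then mixes the tracker's effect with the difference in volunteers.

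This contrast deserves care because, by the article's own account, each intervention's effectiveness can be judged only as a single-group pre-post change. The comparison between groups is the only one that randomisation can protect.

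**Working it through.** **1. Sequence.** Setting the two sections side by side gives: manager consent; team randomisation; arm-dependent recruitment material; information session; eligibility check; individual consent; baseline activPAL week; baseline questionnaire; tracker handed out. Everything that determines which individuals are analysed comes after allocation. What precedes it is team selection and manager consent, so selection of teams is protected and selection of individuals within teams is not.

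**2. Room for a difference.** If about two-thirds enter, about one-third do not, so uptake can differ between arms.

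**3. The plan's own figures.** Inputs from Sample Size and Table 2: 75 per group, 30% attrition, ICC 0.1, average 5.83 per team, SD 90, pre-post correlation 0.6.

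- Design effect: 1 + 0.1 × 4.83 = 1.483.
- Effective number per group: 75 × 0.7 / 1.483 = 52.5 / 1.483 = 35.4.
- SD of change: 90 × √(2 × (1 − 0.6)) = 80.5 minutes.
- Power for a within-group change of 45 minutes: 89.8% (noncentral t); stated 90%.
- Between-group standard error: 80.5 × √(2/35.4) = 19.1 minutes for change scores. With baseline adjustment the SD is 90 × √(1 − 0.36) = 72, and the standard error is 17.1 minutes.
- Detectable difference at 80% power, (1.96 + 0.84) × SE: 53.6 and 47.9 minutes; the stated 50 lies between them.

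The stated figures reproduce. The concern is about order, not arithmetic.

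**4. Possible size (assumed values).** Let *q* be the difference between arms in the share of volunteers with some trait that the adjustment does not capture, and *D* the extra change in sitting among those who have it. Bias = *q* × *D*, in minutes:

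| *q* | *D* = 15 | *D* = 30 | *D* = 45 |
|---|---|---|---|
| 0.10 | 1.5 | 3.0 | 4.5 |
| 0.20 | 3.0 | 6.0 | 9.0 |
| 0.30 | 4.5 | 9.0 | 13.5 |

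One way to reach *q* = 0.20 is uptake of 60% in one arm and 75% in the other: (75 − 60)/75 = 0.20 of the larger arm would be extra recruits. With *D* = 45 the bias is 9 minutes, and 9/50 = 18% of the detectable difference.

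**5. Effect on the test.** With standard errors of 19.1 and 17.1 minutes, the two-sided 5% false-positive rate becomes:

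- bias 4.5 minutes: 5.6% to 5.8%;
- bias 9 minutes: 7.6% to 8.2%;
- bias 13.5 minutes: 10.9% to 12.4%.

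A larger sample would shrink the standard error but not the bias.

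**6. What adjustment can do.** It handles measured differences only. The baseline activPAL week and the questionnaire that follows it are both completed after allocation, so the covariates themselves are not collected blind to arm.

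**The case against.** Several points on the other side stand.

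- The contrast is a secondary aim of a pilot, and the Discussion calls it preliminary. The primary aims are feasibility, acceptability and within-group change at 3 months. For these, the ordering mainly affects who is represented in each group.
- The eligibility criteria are largely factual (work fraction, ability to walk, pregnancy, tape allergy, planned absence, own workstation), so unblinded screening leaves little discretion. The more plausible route is self-selection.
- The article collects technology confidence, use of other apps or wearables, and sitting and standing preference, and names them as candidate confounders for relative effectiveness. Participation is a planned feasibility measure. Part of the protection therefore exists.
- Wearers cannot extract their activPAL data, which limits reactivity in the baseline week.

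A reader might also infer more than the text supports:

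- *That randomisation no longer protects the comparison at all.* Teams are still randomly allocated within strata, using a schedule created by someone outside the study. Only individual uptake is exposed.
- *That Group 1 members decline or join knowing they will get no tracker, or that Group 2 members join knowing they may keep theirs.* The article does not say what Group 1 is told, and it mentions keeping the device without saying that recruitment material does.
- *That phone access separates the arms.* A sufficient number of members with a suitable phone is required of every team before randomisation. This limits that route, though there is no individual phone criterion.
- *That the bias is about 9 minutes, or favours the tracker.* The uptake and response values are assumed, *D* = 45 equals the plan's whole minimum difference of interest, and the direction is unknown.

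None of this removes the point. Adjustment is partial, and the limitation is not stated.

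**Conclusion.** The concern holds for the between-group contrast. The article itself states that allocation precedes individual screening, consent and baseline, that recruitment material differs by arm, and that nobody is blinded. Individual uptake can therefore differ by arm, and the planned adjustment only partly deals with this.

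Whether such a difference occurred, and in which direction, cannot be told from the document. Under the assumed ranges the bias is 1.5 to 13.5 minutes, or 3% to 27% of the 50-minute detectable difference. At the lower end it hardly matters; at the upper end it roughly doubles the false-positive rate. This is an unacknowledged limitation of a secondary comparison. It does not invalidate the pilot or its primary within-group aims.

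**What to change.** **For the design (a later trial, or any team not yet recruited).** Send every team the same information sheet describing both conditions. Complete eligibility, consent, the baseline activPAL week and the baseline questionnaire for a team, and only then disclose its allocation, when the booklet and LUMOback are distributed. Trackers are already handed out only after baseline, so this reorders existing steps. Planned numbers and power do not change. The costs are small: Group 2 gets set-up information later, and Group 1 learns that the tracker exists, which adds slightly to the contamination risk the article already recognises.

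**For this trial, where data collection has finished.**

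1. Report the numbers invited, eligible and consented, and baseline characteristics, by arm and by team.
2. Adjust the contrast for a fixed set of covariates, using their baseline values (for example technology confidence, use of other wearables, sitting and standing preference), in place of retention at P<.2.
3. State in the limitations that individuals were recruited after team allocation was known, and that the between-group contrast is open to recruitment bias which adjustment may not remove.

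This needs no new data beyond the recruitment records and measures the article already describes.
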